### Sample size

The sample volume was calculated at the confidence level of 95%, the power of the test was 80%, and according to the information of the article by Kurdi et al. (16) with values of  $\sigma_1=1.5$ ,  $\mu_1=5$ ,  $\sigma_2=2.2$ , and  $\mu_2=6.4$ , with the following formula and assuming dropout During the implementation, the number of 36 samples in each group is estimated.

$$n = \frac{(Z_{1-\alpha/2} + Z_{1-\beta})^2 (S_1^2 + S_2^2)}{(\mu_1 - \mu_2)^2}$$

### Statistical analysis

The analysis method used in this study is intention-to-treat analysis, ensuring the maintenance of the random allocation process. After collecting the data in the first stage, the basic variables of the patients in the intervention and control groups will be compared to ensure the desirability of the random allocation process. SPSS version 20 software and ANOVA, chi-square, repeated measurements and multilevel mixed-effects linear regression will be used to analyze the primary results. For comparing pain intensity and episiotomy wound healing after the intervention in the 3 groups, the analysis of covariance (ANCOVA) test will be used, taking into account the measurements taken prior to the intervention. Multilevel linear regression will be conducted to adjust for confounding variables, including demographic, midwifery, and delivery-related factors. Additionally, the effect size will be demonstrated through mean differences and 95% CIs. A significance level of  $P < 0.05$  will be considered as the threshold for statistical significance

### Data Collection and Management

This research will be conducted after obtaining permission from the Ethics Committee of Babol University of Medical Sciences, registering with the Iranian Registry of Clinical Trials, and obtaining the necessary sampling permits. After contacting the midwifery department of the hospitals affiliated with Babol University of Medical Sciences, the researcher invites eligible women to participate in the study. The researcher will first explain the study's purpose and the nature of the intervention to the women. The researcher ensures the confidentiality of their information, clarifies her responsibility for any treatment complications, and assures them that the treatment interventions will not change if they choose not to participate. Then, by obtaining the informed consent of the qualified, she will conduct convenience sampling.

Entry criteria for this study: primiparous women, natural vaginal delivery with episiotomy, literacy, and BMI < 30.

Exclusion criteria from this study: unwillingness of participants to continue participating in the study, fourth-degree tear, history of dermatitis, history of allergy and eczema diagnosed related to plants, and history of gestational diabetes and overt diabetes.

The researcher will select and randomly assign the samples to two intervention groups and one routine care group according to the study entry criteria. Eligible people are placed in one of three groups A: 36 people, B: 36 people, and C: 36 people, using permuted block randomization and open label. 18 blocks of 6 will be produced to create a sequence of size 108. In order to keep the random allocation list secret, a special code will be assigned to each of the intervention groups, which only the main implementer of the project will be aware of. Also, the second moderator, who is a student and study evaluator, and the person who performs the statistical analysis, will not know about the codes assigned to the drugs. The intervention group consisted of two groups of mothers, one group will receive black seed and olive oil and the other group will receive olive oil alone. To prepare the product, cold-pressed black seed oil is used, as well as standard extra-virgin olive oil (according to the national standard). Standard extra virgin olive oil is prepared by a company with pharmaceutical grade (Pisgaman Chemi). Cold-pressed black seed oil is obtained from pharmaceutical company (Barij Essential Oil). Both oils are mixed in equal proportions and packaged (29). Both products have approved specifications in terms of microbial and pollution control standards, chemical and physical control. The process of mixing and packaging of two oils is done under hygienic conditions in the traditional pharmacy laboratory of the Faculty of Traditional Medicine. All study subjects will be educated on following post-delivery health tips and caring for episiotomy wounds. The intervention groups (one group receiving olive oil plus black seed oil and the other receiving olive oil alone) will also receive instructions on how to use the containers containing the oils. Women in the intervention groups will use the oils 24 hours after delivery, applying 10 drops topically 3 times a day for 10 days (12). The participants will be instructed to wash and dry their perineum before applying the oils. They should then wear gloves and slowly apply 10 drops of oil to the perineum, massaging it in with their hands. The control group will receive only routine care. The researcher also examines the severity of perineal pain and episiotomy wound healing in both groups, the first 24 hours after delivery and ten days after that. Given that each milliliter contains 15 drops, and mothers are required to use the oils 3 times a day, approximately 30 mL of each type of oil will be provided to mothers for the duration of 10 days. To measure the intensity of episiotomy pain, a 10-cm pain ruler scale (6, 12) will be used, the zero mark of which means no pain and the mark of 10 is the worst possible pain. Episiotomy wound healing will be assessed by the researcher using the Rida scale (6, 12, 17). In this way, the participant will be placed in a lithotomy position and the variables of redness, edema, ecchymosis, discharge and approximation between the two edges of the episiotomy wound will be scored based on the REEDA scale (12).

Secondary outcomes include the monitoring of symptoms such as burning and itching, as well as the occurrence of episiotomy opening and the need for painkillers. These secondary outcomes will be assessed through a combination of examinations conducted by the researcher and self-reports provided by the mothers. Additionally, any side effects reported by each participant will be carefully reviewed, and the total number of side effects within each group will be documented.

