**Possible implementation problems**

Not using sterile tape and using eye examination.

Some mothers may not come for examination on the 10th day. (For example, due to hospitalization of the baby)

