## Ethical considerations

- Necessary permission will be obtained from the research ethics committee of the honorable research vice president of the university in order not to contradict the study with research ethics.
- By obtaining a written letter of introduction from Babol University of Medical Sciences, the researcher will introduce himself to the relevant officials of the hospitals covered by the university.
- The researcher will clearly present his goals to the officials of the medical centers and the subjects of the research, verbally and in writing, and will get permission to conduct the research.
- Written consent will be obtained from the people participating in the research.
- Subjects will be free to agree or disagree to participate in the study or withdraw from it.
- All people participating in the research will be assured of the confidentiality of their information, and they can leave the study for any reason, such as choosing other methods of episiotomy wound care during the research.

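### Unwillingness to continue is listed as an exclusion criterion, so women can be removed after allocation, which conflicts with the stated intention-to-treat analysis

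*Protocol*

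**What the plan says.** The section Data Collection and Management has one exclusion list, which begins: "Exclusion criteria from this study: unwillingness of participants to continue participating in the study". The remaining items (fourth-degree tear, dermatitis, plant-related allergy or eczema, diabetes) are conditions that exist before entry. Just before the list, the same section says: "Then, by obtaining the informed consent of the qualified, she will conduct convenience sampling". Allocation is then described as "A: 36 people, B: 36 people, and C: 36 people, using permuted block randomization and open label".

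Statistical analysis states: "The analysis method used in this study is intention-to-treat analysis, ensuring the maintenance of the random allocation process". It names ANCOVA with the pre-intervention value for comparing pain and wound healing between the three groups, and also lists repeated measurements and multilevel mixed-effects regression.

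Two other sections bear on who will have outcomes. Ethical considerations says of participants that "they can leave the study for any reason, such as choosing other methods of episiotomy wound care during the research". Possible implementation problems warns: "Some mothers may not come for examination on the 10th day". Pain and REEDA, the two primary outcomes, are each measured once at baseline (first 24 hours) and once after it (day 10).

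**The concern.** Every other item in the list can be checked before a woman is allocated. This one cannot: she can be unwilling to continue only once she has entered. An exclusion rule triggered by what happens after allocation takes women out of the randomised comparison, and intention-to-treat analysis exists to prevent that. The example in Ethical considerations makes matters worse, because it turns a change of wound care into a departure from the study, and so into a missing outcome.

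At stake is validity more than power. Women know their arm. A woman in pain under routine care has a motive to try something else, and an oil user with burning or itching (which the protocol monitors) has a motive to stop. A woman who has healed may see no reason to attend on day 10. Loss of control women with much pain would shrink an apparent benefit, and loss of oil users who fare badly would inflate it, so the direction cannot be known in advance. Both primary outcomes are exposed.

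**Working it through.** **Reading the sections together**

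1. Refusal to join is dealt with by consent, which precedes sampling and allocation. The exclusion item therefore concerns women already entered.
2. Some could change their minds between consent and allocation. With outcomes running to day 10, most of the time in which a woman can become unwilling lies after allocation.
3. Statistical analysis promises intention-to-treat. No section says that women who stop are still followed or still analysed.
4. With a single post-baseline assessment, a woman without a day-10 value contributes nothing to an ANCOVA of day-10 scores on baseline. The mixed-effects model does not help if she has been excluded from the study.

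**The plan's own sample size**

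Inputs from Sample size: means 5 and 6.4, SDs 1.5 and 2.2, 95% confidence (two-sided, since the formula uses 1 − α/2), power 80%, 36 per group including dropout at an unstated rate.

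- n = (1.960 + 0.842)² × (1.5² + 2.2²) / (5 − 6.4)² = 7.849 × 7.09 / 1.96 = 28.39, rounded up to 29 per group.
- Implied allowance: 1 − 29/36 = 7/36 = 19.4%.
- Check: an assumed 20% loss gives 28.39 / 0.8 = 35.5, rounded up to 36, which matches the plan. Assumed rates of 10% to 25% applied to 29 give 33 to 39.
- Normal-approximation power is 88% with 36 evaluable per group and 81% with 29. The allowance therefore protects power. It does nothing about bias.

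**Size of the bias (assumptions, not figures in the protocol)**

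If a fraction d of one arm leaves, and the leavers' mean differs by g from the stayers' mean, the observed mean of that arm shifts by d × g.

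| Scenario, one arm only | Shift in arm mean | Share of the planned 1.4 |
|---|---|---|
| Loss at random (g = 0) | 0 | 0% |
| d = 0.194, g = 1 point | 0.19 | 14% |
| d = 0.194, g = 2 points | 0.39 | 28% |
| The 7 control women with most pain leave | 0.75 | 54% |

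The last row treats control scores as normal with SD 2.2 and removes the top 7/36 (cut-off z = 0.862, normal density there 0.275): 2.2 × 0.275 / (29/36) = 0.75, and 0.75 / 1.4 = 54%. With a control mean of 6.4, those seven women would average 6.4 + 2.2 × 0.275 / 0.194 = 9.5 on a 0 to 10 ruler, so this is an extreme bound. Sample size does not label its two means by arm; taking 6.4 and 2.2 as the control arm is an assumption.

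**The case against.** The strongest reply is that exclusion from the study is not exclusion from the analysis. The protocol never says that data are deleted, the sentence that governs the analysis says intention-to-treat, and a right to withdraw is one that any trial must grant. The item may be a loosely worded reference to ending follow-up, which can coexist with intention-to-treat. This stands in part. A reader might infer that the protocol orders these women's data to be discarded and a completers' analysis to be done; it does not say so. But the item sits in an exclusion list, nothing limits it to the gentler reading, and no other text retains these women.

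Further points on the other side stand as limits:

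- Mixed-effects regression is among the named methods, so the protocol does not commit to complete-case ANCOVA alone.
- Imputation and sensitivity analyses are commonly left to an SAP, which is not at hand. Their absence is no finding.
- The control group receives routine care, and all women are taught wound care. It is not an untreated group.
- The 54% figure is one-sided. It assumes selective loss in one arm only, among exactly the women with the worst scores.

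None of these removes the conflict between an exclusion rule triggered after entry and the declared analysis.

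**Conclusion.** The concern holds as a conflict in the protocol's own text: a rule that excludes women after entry stands beside a promise to maintain the random allocation, and nothing reconciles the two. On illustrative assumptions (19% leaving one arm, mean pain 1 to 2 points from those who stay), that arm's mean moves by 0.19 to 0.39 points. The bound of 0.75 should not be read as an expected bias, and if loss is unrelated to outcome the bias is nil. The 19% is back-calculated from 29 and 36, not stated by the plan. The documents support neither a claim that the analysis will certainly be of completers nor a claim about the direction of the bias. No change in sample size follows. The wording should be settled before enrolment, because a day-10 outcome that is not collected cannot be recovered later.

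**What to change.** 1. Take unwillingness to continue out of the exclusion criteria and put it in a separate withdrawal paragraph.
2. State there that stopping the oil, or using other wound care, does not by itself end follow-up, and reconcile the sentence in Ethical considerations with this. The right to withdraw is unchanged.
3. State in Statistical analysis that all randomised women are analysed in the arm to which they were allocated.
4. Unless consent to follow-up is withdrawn, seek the day-10 outcomes of women who stop or do not attend, taking the 0 to 10 pain score by telephone if needed.

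The choice of missing-data method can be left to the SAP. The daily checklist is no substitute source for pain, since it is described as covering the secondary outcomes only.

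The cost is protocol wording and a few calls. There are two small limits: a spoken score is not the same as a mark on a ruler, and REEDA needs an examination, so a missed wound assessment cannot be recovered by telephone.

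### Unwillingness to continue is an exclusion criterion, and stopping the assigned care is not separated from ending follow-up; as written this conflicts with the declared intention-to-treat analysis

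*Protocol*

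**What the plan says.** Three places in the protocol bear on this.

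- *Data Collection and Management*, eligibility paragraph: "Exclusion criteria from this study: unwillingness of participants to continue participating in the study". The rest of the list is baseline history or delivery findings: fourth-degree tear, dermatitis, plant-related allergy or eczema, and diabetes.
- *Ethical considerations*: participants are told that "they can leave the study for any reason, such as choosing other methods of episiotomy wound care during the research".
- *Statistical analysis*: "The analysis method used in this study is intention-to-treat analysis, ensuring the maintenance of the random allocation process".

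The primary outcomes, pain on the 10-cm scale and REEDA, are measured at "the first 24 hours after delivery and ten days after that". There is therefore one measurement after the intervention. The sample size section reaches its figure "assuming dropout During the implementation, the number of 36 samples in each group is estimated", with no rate given. *Possible implementation problems* adds that "Some mothers may not come for examination on the 10th day". The document does not say whether a woman who stops the oil, or turns to another method, is still examined on day 10.

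**The concern.** Eligibility criteria decide who is randomised. A criterion that can be met only after randomisation decides who stays in, and intention-to-treat exists to prevent that. The ethics wording adds to the problem because its one example of a reason for leaving is a change of treatment. Under intention-to-treat, a woman who changes treatment is followed and analysed in her allocated arm.

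The design makes this matter. The trial is open label, one arm receives routine care only, and pain is self-reported. Plausible reasons for stopping or switching are persistent pain, burning or a poorly healing wound. These are the trial's outcomes or close to them, and they need not be equally common in the three arms. If such women go without a day-10 score, those who remain look better than those who were randomised. The comparison then shifts according to which arm loses more.

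An analysis plan cannot repair this later, because it cannot restore day-10 examinations that were never made.

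**Working it through.** **1. The text.** *Continue* presupposes participation. Refusal to join is handled separately in the same section, through consent and the assurance to women who choose not to take part. Assignment follows the entry criteria, and the oils are used for 10 days after that. The first exclusion criterion therefore acts after randomisation, whereas the *Statistical analysis* section promises that the random allocation is maintained. As written, both cannot hold for a randomised woman who stops but could still be examined.

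**2. The plan's own sample size.** Inputs from *Sample size*: two-sided 5%, power 80%, means 5 and 6.4, SDs 1.5 and 2.2.

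n = (1.960 + 0.842)² × (1.5² + 2.2²) / 1.4² = 28.39, so 29 per group.

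The stated 36 follows from an assumed dropout of about 20%: 28.39 / 0.80 = 35.5. The implied allowance is 1 − 29/36 = 19.4%, or seven women per arm.

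**3. Illustration of size.** Assumptions, none of them in the protocol:

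- Scores are normal.
- The group with mean 6.4 and SD 2.2 is routine care.
- 20% of one arm is lost, so 29 v 36 are analysed.
- Leaving depends on day-10 pain.
- The analysis is a simple comparison of means.

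*Extreme case: all of the worst 20% leave.* With c = 0.842 and φ(c) = 0.280, the mean falls by 2.2 × 0.280/0.80 = 0.77. The remaining SD is 2.2 × √(1 − 0.842 × 0.350 − 0.350²) = 1.68.

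*Milder case: the odds of leaving double per SD of worse pain, with 20% leaving overall.* By numerical integration, the women who stay average 0.129 SD better: 2.2 × 0.129 = 0.28. The remaining SD is 2.13.

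Power = Φ(difference/SE − 1.96):

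| Loss | Difference | SE | Power |
|---|---|---|---|
| None, 36 v 36 | 1.40 | √(7.09/36) = 0.444 | 88% |
| Routine care, at random, 29 v 36 | 1.40 | √(2.2²/29 + 1.5²/36) = 0.479 | 83% |
| Routine care, milder case | 1.40 − 0.28 = 1.12 | √(2.13²/29 + 1.5²/36) = 0.468 | 67% |
| Routine care, extreme case | 1.40 − 0.77 = 0.63 | √(1.68²/29 + 1.5²/36) = 0.400 | 35% |

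The smaller number alone takes power from 88% to 83%. The rest of the fall comes from selective loss.

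**4. Other patterns of loss.**

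- *10% lost instead of 20%:* shifts of 2.2 × 0.066 = 0.15 (milder) to 2.2 × 0.195 = 0.43 (extreme).
- *Worst 20% lost from an oil arm only (SD 1.5):* that mean falls by 1.5 × 0.350 = 0.525, and the apparent difference rises to about 1.92.
- *Equal 20% loss from both arms:* the difference becomes 1.40 − 0.28 + 0.19 = 1.31 (milder) or 1.40 − 0.770 + 0.525 = 1.155, about 1.16 (extreme).

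Loss from routine care hides an effect and loss from an oil arm exaggerates one, so the direction is not predictable.

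**The case against.** A reader might infer that the protocol removes women whose assigned care failed, or that switching wound care automatically ends participation. The documents support neither. The ethics sentence is a right to withdraw with an example attached: it says a woman may leave, not that one who switches must. The exclusion criterion speaks of participating in the study, not of using the oil, so a woman who stops the oil but still attends does not plainly meet it. No sentence says that leavers' data are deleted, and no sentence says why women would switch.

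It can also be said that a woman who refuses all further contact is missing under any plan, that intention-to-treat can coexist with missing data, that the sample size allows for dropout, and that handling of withdrawals may sit in an analysis plan not shown here. This is fair, and it limits the point. The 20% used above is the whole implied allowance, which must also cover missed visits for unrelated reasons such as a baby in hospital. The planned baseline-adjusted ANCOVA may absorb the part of the selection that runs through the first pain score.

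What remains is narrower. An event after enrolment is written as an exclusion, and neither section separates stopping care from ending follow-up. With a single measurement after the intervention, whether a woman who stops is asked back on day 10 is a matter of conduct that the protocol has to settle.

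**Conclusion.** The point holds at moderate severity. The exclusion list and the ethics wording leave open that a randomised woman who stops or changes care is excluded without day-10 outcomes, which conflicts with the declared intention-to-treat analysis. That conflict rests on the text alone.

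The figures only show scale. At 20% loss from one arm with SD 2.2, the false improvement of 0.28 to 0.77 is a fifth to just over a half of the planned 1.4 (0.28/1.4 = 20%; 0.77/1.4 = 55%). The upper end needs every one of the worst-scoring 20% to leave one arm and nobody to leave the other, so it is a bound and not a forecast. At 10% loss, or with equal loss from both arms, the effect is much smaller. How many women would leave, from which arm and for what reason cannot be known from the protocol.

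**What to change.** - *Data Collection and Management*: delete unwillingness to continue from the exclusion criteria.
- *Ethical considerations*: separate two events. A woman who stops or changes her assigned care is still asked to complete the daily checklist and the day-10 pain and REEDA assessments, and is analysed in her allocated arm; any other method used is noted on the checklist. Only withdrawal of consent to follow-up ends data collection.
- Count both events by arm.

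The cost is a few sentences of wording and one line on an existing checklist, with no added participants or visits. The right to leave at any time is unchanged. Women who withdraw consent remain missing, so the change recovers only those willing to be followed. Including women who switched may slightly dilute the estimated effect, which intention-to-treat already accepts. The change needs to be in place before women begin to leave, because missed day-10 assessments cannot be recovered.

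### Fixed blocks of 6 in an open-label trial, with no described independent release of assignments, let a fully informed recruiter foresee up to one allocation in five

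*Protocol*

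**What the plan says.** All of this stands in the protocol's section Data Collection and Management.

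- **Recruitment.** "the researcher invites eligible women to participate in the study", and "by obtaining the informed consent of the qualified, she will conduct convenience sampling". One person therefore has discretion over whom to approach and when.
- **Assignment.** "The researcher will select and randomly assign the samples to two intervention groups and one routine care group". Read literally, this is the same person.
- **List.** Women are allocated to three equal groups of 36 "using permuted block randomization and open label. 18 blocks of 6 will be produced to create a sequence of size 108". A single block size is thereby fixed.
- **Concealment.** The stated measure for secrecy is this: "a special code will be assigned to each of the intervention groups, which only the main implementer of the project will be aware of". The student evaluator and the analyst are not told the codes for the drugs.

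The section describes no sealed opaque envelopes, no central or third-party allocation, no varying block size, and no point in the enrolment sequence at which an assignment is revealed. It does not say who holds the list, or whether one list serves all the hospitals. The routine-care group receives no oil.

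**The concern.** Allocation concealment and masking of treatment are different protections. The code addresses masking: it keeps the evaluator and the analyst from knowing which oil is which. It does nothing to stop a person who follows the sequence from working out what comes next, because coded letters obey the same block pattern as named arms. Routine care is recognisable whatever the code, since those women get no container.

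Convenience sampling alone affects only how representative the women are. It threatens the comparison between arms when the person choosing whom to approach can foresee the arm. Expected pain, the look of the wound or apparent willingness could then influence who enters which group. Both primary outcomes are exposed: pain is self-reported, and REEDA is scored by the researcher. Intention-to-treat analysis, which the protocol plans, preserves the groups after allocation; it does not protect how they were formed.

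**Working it through.** **Inputs (protocol, Data Collection and Management).** Three arms of 36; 18 blocks of 6; open label.

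**The plan's own figure.** 18 × 6 = 108 = 3 × 36, so the sequence length is reproduced. Each block holds 6 / 3 = 2 women per arm, giving 6! / (2! 2! 2!) = 90 equally likely orderings.

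**Assumption for what follows.** The recruiter knows the block size, knows where each block starts, and sees every earlier allocation. An allocation is certain when all places left in the block belong to one arm.

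**Exact arm certain.** At the fifth place two places are left. Of the C(6,2) = 15 possible remaining pairs, 3 are same-arm pairs: 3/15 = 0.200. The sixth place is always certain. Earlier places never are.

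**At least one arm ruled out.** Third place: the first two women are in the same arm, 3/15 = 0.200. Fourth place: the first three are not all different, 1 − 8/20 = 0.600. Fifth and sixth places: always.

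**Oil versus routine care certain.** A block has 4 oil and 2 routine-care places, so 15 orderings. Third place: both routine-care places are used, 1/15 = 0.067. Fourth: 3/15 = 0.200. Fifth: the two left are of the same kind, (1 + 6)/15 = 0.467. Sixth: 1.

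**Best guess of the arm.** This is the expected share of remaining places held by the commonest remaining arm.

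| Place in block | Exact arm certain | An arm ruled out | Oil v. routine certain | Best guess right |
|---|---|---|---|---|
| 1 | 0 | 0 | 0 | 0.333 |
| 2 | 0 | 0 | 0 | 0.400 |
| 3 | 0 | 0.200 | 0.067 | 0.500 |
| 4 | 0 | 0.600 | 0.200 | 0.533 |
| 5 | 0.200 | 1 | 0.467 | 0.600 |
| 6 | 1 | 1 | 1 | 1 |
| Sum per block | 1.2 | 2.8 | 1.733 | 3.367 |
| Share (sum / 6) | 20.0% | 46.7% | 28.9% | 56.1% |
| Expected of 108 (sum × 18) | 21.6 | 50.4 | 31.2 | 60.6 |

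Under simple randomization the best guess would be right 33.3% of the time.

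**Effect of mixed block sizes.** Nine blocks of 6 and six of 9 give 54 + 54 = 108 women, and 9 × 2 + 6 × 3 = 36 per arm. I simulated lists in random order, with a recruiter who updates on every past allocation. The result depends on what that recruiter knows:

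| Recruiter knows | Exact arm certain | An arm ruled out | Best guess right |
|---|---|---|---|
| Sizes 6 and 9 are used, treated as independent draws | 4.2% | 11.5% | 54.7% |
| The exact composition, but not the order | 5.8% | 15.1% | 54.6% |

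Mixing sizes removes most of the certainty (20% to about 4–6%) and most of the exclusion of an arm (47% to about 11–15%). It hardly moves the best guess (56% to about 55%).

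**The case against.** The strongest objection is that every percentage describes a fully informed recruiter, and the protocol does not say that such a person exists. It nowhere states that the recruiter sees the list. Recruitment takes place in more than one hospital; if several recruiters share one list, each sees only part of it and predicts less. If the oil containers carry no letter and look alike to the recruiter, only the contrast of oil with routine care is visible, and the 20% for the exact arm does not apply. The sentence naming the researcher as the one who assigns may be loose wording, since the same paragraph also names a main implementer, a student evaluator and an analyst, and declares that the list is to be kept secret.

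All of this stands as a limit on size. A reader might infer that one allocation in five will in fact be known in advance; the documents do not support that, and the figures are ceilings. The point itself survives. An intention of secrecy is stated, but the mechanism given is a treatment code, which does not conceal the next assignment. The lack of clear roles is part of what needs fixing.

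A second objection is that the analysis offers some protection. The Statistical analysis section plans ANCOVA on the pre-intervention measurements, and a multilevel regression adjusting for demographic, midwifery and delivery-related factors. These would remove some of the bias that acts through measured baseline severity, so it would be wrong to say that nothing can be repaired. They cannot remove selection on unmeasured factors such as willingness.

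**Conclusion.** The concern holds as a weakness in allocation concealment that should be corrected. The main gap is that no independent release of assignments after enrolment is described; the single fixed block size makes it worse. The ceiling is 20% of allocations certain as to exact arm (about 22 of 108), 29% certain as to oil versus routine care (about 31 of 108), and 47% with at least one arm ruled out (about 50 of 108). These rest on a recruiter who knows the block size and follows all past allocations on one list. That is plausible, because the size is written in the protocol, the trial is open label, and the researcher is said to assign.

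It would go too far to conclude that selection has happened or that the results would be biased. The documents show an opportunity only, and baseline adjustment would offset part of any effect.

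**What to change.** 1. **Separate release from recruitment (the main change).** State that the main implementer does not recruit, holds the list, and releases each assignment only after consent, eligibility and baseline VAS and REEDA have been recorded. Say which role recruits, which assigns and which assesses, and whether one list serves all hospitals.
2. **Vary the block size (in addition).** Replace the 18 blocks of 6 with a randomly ordered mix whose sizes are withheld from the recruiter, for example nine blocks of 6 and six of 9. This alone is not enough, because the best-guess rate stays near 55%.

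The cost is a new list, a release step for each woman, and slightly larger temporary imbalance between arms during recruitment. The total of 108, the 36 per arm and the planned analysis do not change.
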